## Trial documentation, schedule and follow-up

### Documentation and follow-up

#### First Visit

Before treatment the general medical history report forms have to be filled out including the following items:

anamnesis (height, weight, general condition, Karnofsky index, medical history)

Localization of the tumor (mammography, ultrasound), if palpable (drawing)

histology (if already available)

quality of life assessment

- photo documentation (3 pictures, at 1 m distance—arms/hands on hips en face, and arms elevated en face + lateral from side of surgery)

#### Follow up

Follow-up visits will be scheduled after 6 weeks, 4.5 months, 6 months and annually after radiotherapy. Photographic documentation and assessment of quality of life will be performed at follow-up visits as well as documentation of general condition, weight, new symptoms according to CTC and LENT SOMA score. Furthermore mammography and ultrasound of the breast will be performed according to international guidelines.

Acute side effects in patients, who received postoperative WBRT, will be documented by the CTC score.

The follow-up and documentation of patient specific data will end after 10 years after therapy.

### Protocol deviation

Every protocol deviation has to be defined and documented for every patient.

The investigator has to consult the principle investigators, to discuss the type and amount of deviation and their possible consequences for the patient.

## Assessment of efficacy parameters

### Relapse

At each follow-up visit there will be a clinical examination to assess local relapse (within 2 cm around the tumor bed) by palpation. Relapses more than 2 cm distant from the tumor bed will count as an ipsilateral relapse. Therefore mammography and ultrasound of the breast will be performed according to international guidelines.

### Quality of life

To assess the quality of life two standardized, validated questionnaires of the EORTC (QLQ-C30 version 3.0 and BR23) will be used before IORT and documented during follow-up visits. The two questionnaires contain 53 questions and require about 10 minutes to be completed.

## Assessment of safety parameters

Classification and graduating of side effects are rated by “Common Toxicity Criteria” (CTC) of the National Cancer Institute (Bethesda/USA). If necessary photo documentation should capture acute toxicities to give suitable follow-up. The acquisition of late toxicities will be done based on the LENT SOMA score.

### Serious adverse events (SAE)

Serious adverse events (SAEs) are defined as any event that is fatal, life threatening, causes or prolongs hospitalization; causes disability or incapacity or requires medical intervention to prevent permanent impairment or damage, or any grade 4 toxicity.

In case of death an autopsy should be done to clarify the cause of death.

Regarding the comorbidity of elderly patients only radiation related SAEs (rrSAEs) grade 4 and 5 including date and on-/offset should be reported. Furthermore rrSAEs requiring therapy should be documented (e.g. antibiotics, aspiration).

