**Discussion:**

It is a pragmatic trial in which each participating centre has the option to modify entry criteria and criteria for WBRT according to this core protocol after consultation with the steering committee and local ethics committee (e.g. size, free margins). Only centers with access to the Intrabeam system (Carl Zeiss) can recruit patients into the trial.

Its aim is to confirm the efficacy and toxicity of IORT in a well selected collective of elderly patients with breast cancer.

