### Post-pathology stratum

Patients will be recruited for entry to the trial only once the pathological characteristics of the tumor have been reported. These patients will have local surgery as per usual practice and if the patient and the tumor fit in the criteria defined in the protocol and the investigator’s treatment policy, she will be asked for consent to enter the trial and if given she will have further surgery at which the wound is opened, the probe inserted and the radiation dose given. This stratum of patients addresses a much more explanatory question as their entry to the trial will be strictly defined on pathological grounds. However, the disadvantage for these patients is that they must have a second surgery. Including these patients will allow an assessment of the local control obtained in very good prognosis patients.

This strategy also allows for the entry of patients who have already received surgery at an outlying centre. The post-pathology stratum will recruit 270 patients.

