#### Investigator withdrawal

The steering committee is allowed to close the study ahead of schedule.

Other stop-criteria might be:

Insufficient recruitment

Unexpected high toxicity

Any grade V toxicity

More than 3 grade IV toxicities within the first 20 patients

More than 5 grade IV toxicities within the first 50 patients

Ethical and medical considerations with regard to new evidence (benefit/risk ratio).

More than 5 local relapses after the first safety report

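### SAE reporting covers only radiation-related grade 4–5 events, so a non-fatal grade 4 surgical or anaesthetic event of the second operation that delivers IORT need not be reported

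*Protocol article*

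**What the plan says.** The section on serious adverse events first defines an SAE broadly, by outcome and severity. The definition includes life-threatening events and any grade 4 toxicity, and it sets no causality condition. The section then narrows what has to be reported. Giving comorbidity in elderly patients as the reason, it says that "only radiation related SAEs (rrSAEs) grade 4 and 5 including date and on-/offset should be reported". The sentence that follows stays within the same class of events: "Furthermore rrSAEs requiring therapy should be documented (e.g. antibiotics, aspiration". The term 'radiation related' is not defined. For deaths the section adds: "In case of death an autopsy should be done to clarify the cause of death".

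The section on the post-pathology stratum describes how IORT reaches those patients. After usual surgery, the pathology report and consent, "she will have further surgery at which the wound is opened, the probe inserted and the radiation dose given". It names the burden openly: "However, the disadvantage for these patients is that they must have a second surgery". This stratum is to recruit 270 of the 540 patients.

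The abstract's Discussion gives toxicity as part of the purpose: "Its aim is to confirm the efficacy and toxicity of IORT". The Follow up section provides for "documentation of general condition, weight, new symptoms according to CTC and LENT SOMA score" at visits that begin 6 weeks after radiotherapy.

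**The concern.** For half of the planned patients the trial treatment is radiation plus an extra operation with its anaesthesia. The reporting rule covers only the first component. An embolism, a cardiac event or a bleed after the second operation could be life threatening, be caused by a procedure the patient underwent only because she joined the trial, and still fall outside the rule because radiation did not cause it.

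The stated reason does not reach this case. Comorbidity explains why one would not want every hospital admission of a woman over 70 reported. It does not explain leaving out harm from a study procedure, and operative harm matters more in a population with comorbidity. What is at stake is the completeness of the serious safety data for a trial that names toxicity in its aim, and consistency between sites, since the same event is reportable or not depending on how a site reads an undefined term.

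**Working it through.** The article states no figure on this point, so there is nothing to reproduce. The check consists of setting the sections side by side and following one event through them: a non-fatal grade 4 event of the second operation or its anaesthesia, not caused by radiation.

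1. **Is it an SAE?** Yes. The definition in the SAE section has no causality condition, and a life-threatening event qualifies.
2. **Must it be reported as an SAE?** No. The reporting sentence contains the word 'only' and requires that the event be radiation related. The sentence on events requiring therapy carries the same condition.
3. **Is the operation part of the trial treatment?** Yes. The post-pathology section places it after trial consent, for insertion of the probe and delivery of the dose.
4. **Is the event captured elsewhere?** In part:
   - *Wound events.* Antibiotics and aspiration, given as examples of therapy, suggest that some infections and fluid collections are counted as radiation related.
   - *Deaths.* These are seen through overall survival and the autopsy request.
   - *Symptoms.* The Follow up section records new symptoms by CTC from week 6 and does not limit this to symptoms still present. The safety section grades side effects by CTC without a radiation condition. Neither is a duty to report the event as an SAE with its date, onset and end.
5. **What remains?** Mainly non-fatal systemic events of the procedure, which have no stated SAE route.

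**Exposure.** 270 / 540 = 50% of planned patients. This is the number exposed to the operation, not a number of events.

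**Stop criteria.** The section on investigator withdrawal introduces its list with "Other stop-criteria might be", so the criteria are discretionary. More than 3 grade IV toxicities in the first 20 patients means at least 4 / 20 = 20%. More than 5 in the first 50 means at least 6 / 50 = 12%. As an illustration only, assume a grade 4 rate of 1–2% per second operation (not in the document) and let all first patients be post-pathology. The binomial probability that operative events alone reach the count is then 0.00004–0.0006 for the first 20 patients and 0.00001–0.0005 for the first 50. Leaving such events out would practically never change a stopping decision.

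**Efficacy.** The primary endpoint is local relapse, which does not use SAE reports.

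**The case against.** The strongest reply is that 'radiation related' is undefined and may be meant broadly. Treatment by antibiotics and aspiration points to wound complications, so the term could cover the whole delivery of IORT, in contrast to comorbidity. That reading is possible for wound events. It does not extend naturally to anaesthetic or systemic events, and a reporting duty should not depend on sites stretching a word.

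Second, the restriction is deliberate and reasoned, and cardiac events or emboli at this age are hard to attribute. This stands as a reason to keep a causality condition. It is no reason to limit the condition to radiation.

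Third, a condensed article may leave perioperative forms to the full protocol. That would excuse silence, but this is an explicit rule, and a full protocol that agrees with it has the same gap.

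Fourth, the fix still leaves sites to separate operation from comorbidity. That is true, and it is a limit of the remedy.

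A reader might also infer more than the document supports:
- *That serious surgical harm goes unrecorded altogether.* It does not: deaths, some wound events and symptoms at visits have other routes.
- *That a number of missed events can be given.* Any such number needs an assumed complication rate and an assumed grade 4 share. A count of all grade 4–5 events would also include deaths and wound events seen elsewhere.
- *That the pre-pathology stratum has the same gap.* There IORT is given during primary surgery, and no separate operation is added for it.

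**Conclusion.** The point holds in a narrow form. The SAE rule leaves a non-fatal grade 4 surgical or anaesthetic event of the post-pathology operation outside mandatory SAE reporting unless the site judges it radiation related, and the stated reason does not justify that. The only documented measure of size is exposure: 270 of 540 planned patients, all aged 70 or older. The number of unreported events cannot be derived from the document.

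A reader might conclude that the trial's safety monitoring or its result is compromised. The document does not support this: the efficacy analysis is not affected, and the stop criteria practically are not. The conclusion rests on reading 'radiation related' in its ordinary sense; a fuller document that defined the term to include the delivery operation would remove it. The point is a cheap improvement, not a defect that threatens the trial.

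**What to change.** In the reporting sentence of the SAE section, replace the radiation condition so that grade 4 and 5 SAEs are reported when they are *related to radiation or, in the post-pathology stratum, to the second operation and its anaesthesia*. Keep the grade threshold, and state that events due only to comorbidity remain excluded. The discontinuation criteria need no change.

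The cost is a wording change in the protocol and the case report form, and a few extra SAE reports, whose number the document does not allow one to derive. No visits or procedures are added. Sites must still judge causality, now between the operation and comorbidity, so some variation between sites will remain.

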## Statistical calculations for trial sample size

### Study hypothesis

This study is designed to confirm the non-inferiority of IORT in comparison to WBRT in elderly patients with low risk breast carcinoma.

Power calculations with an alpha set at 0.01, a beta set at 0.05 (power 95%), and an anticipated drop-out rate of 20% and a loss to follow-up of 20% result in 540 patients to be included. Calculations of the sample size were performed as described by A’Hern
[8], Simon
[9] and Fleming
[10]. Each stratum has to recruit at least 270 patients.

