**Methods/Design:**

This prospective, multicentric single arm phase II study is based on the protocol of the international TARGIT-A study. The TARGIT-E study should confirm the efficacy of a single dose of intraoperative radiotherapy (IORT) in a well selected group of elderly patients with small breast cancer and absence of risk factors. Patients will receive IORT (20 Gy with Intrabeam system/Carl Zeiss) during breast conserving surgery. In presence of risk factors postoperative WBRT will be added to complete the radiotherapeutic treatment according to international guidelines. Endpoints are the local relapse rate (within 2 cm of the tumor bed), ipsilateral in breast relapse, cancer-specific and overall survival and contralateral breast cancer as well as documentation of quality of life and cosmetic outcome.

The expected local relapse rates are 0.5/1/1.5% after 2.5/5/7.5 years, respectively. Discontinuation of the trial is scheduled if rates of local relapse rates rise to 3/4/6% after 2.5/5/7.5 years. Power calculations result in 540 patients with a calculated dropout rate of 20% and loss to follow-up of 20%, an alpha of 0.01 and a beta 0.05. There will be a pre- and a post-pathology stratum (n = 270 each).

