### Description of the primary efficacy analysis and population

A single group of patients is studied. The proportion of patients who respond to treatment (i.e. local relapse free) will be used to estimate the true response rate with a 95% confidence interval. A response rate of 99.5%/99%/98.5% at 2.5/5/7.5 years is anticipated. A response rate of 97%/96%/94% is considered to be the minimum level.

Therefore, efficacy analyses will be performed at two stages.

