### Planned interim analysis

The first after 144 patients and the second after 386 patients were treated. The expected local recurrence rate is 0.5/1/1.5% after 2.5/5/7.5 years, respectively. Stopping rules for the study are if the local recurrence rate is higher than 3/4/6% after 2.5/5/7.5 years. Therefore the efficacy of IORT will be rejected if more than 5 or > 8 patients show a local relapse, respectively.

An interim analysis of late breast toxicity is planned after a two-year follow-up of the first 144 patients. Results will be presented as frequency tables.

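### At the stated alpha of 0.01 and power of 95%, 540 patients do not cover two separate 20% losses, except on the 7.5-year rates

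*Protocol article*

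**What the plan says.** Under Study hypothesis, the protocol article sets alpha at 0.01 and beta at 0.05 and states that "an anticipated drop-out rate of 20% and a loss to follow-up of 20% result in 540 patients to be included". The Methods/Design part of the abstract repeats 540 with the same two 20% figures. The method is given by reference: "Calculations of the sample size were performed as described by A’Hern", together with two further single-arm design papers.

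The section on the primary efficacy analysis supplies the rates. "A response rate of 99.5%/99%/98.5% at 2.5/5/7.5 years is anticipated", and "A response rate of 97%/96%/94% is considered to be the minimum level". As relapse rates, these are 0.5/1/1.5% expected against 3/4/6% unacceptable.

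Planned interim analysis gives two analysis sizes: "The first after 144 patients and the second after 386 patients were treated". It rejects efficacy above 5 relapses at the first and above 8 at the second. Investigator withdrawal also lists a count of more than 5 local relapses, tied to the first safety report.

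The article does not say which landmark drives 540, whether alpha is one- or two-sided, or how the two losses were combined.

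**The concern.** The inputs and the result are both printed, so they can be compared. If 540 is the number recruited and two separate fifths are lost, the number left for the 2.5- and 5-year comparisons is smaller than the stated alpha and power need.

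One of the two error rates must then give way. If the cut-off is set to hold alpha, a treatment with the hoped-for relapse rate is turned down more often than the stated 5%. If the printed limit of 8 relapses is kept, a treatment with the unacceptable rate is accepted more often than the stated 1%. In a single-arm trial of leaving out whole breast radiotherapy, the second error is the more serious.

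**Working it through.** **Inputs.** Alpha 0.01, power 95%, two 20% losses and 540 (Study hypothesis, abstract); relapse rates p0 = 3/4/6% and p1 = 0.5/1/1.5% at 2.5/5/7.5 years (primary efficacy analysis); analysis size 386 and limit of 8 (Planned interim analysis). Assumed: alpha is one-sided, and both losses are complete by the landmark.

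**Where 540 could come from.** Two routes reproduce it.
- 386 × (1 + 0.20 + 0.20) = 540.4. This multiplies where it should divide. To retain 386 one needs 386/0.64 = 603.1, so 604, or 386/0.60 = 643.3, so 644.
- 431/0.80 = 538.75, about 539, or 540 as two strata of 270. At n = 431 a cut-off of 8 relapses first meets alpha 0.01 for 4% against 1% (alpha 0.0098, power 96.9%). This allows for only one of the two losses.

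**Evaluable patients from 540.** Compounded: 540 × 0.8 × 0.8 = 345.6, about 346. Added: 540 × 0.6 = 324.

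**Exact test.** X is the number of relapses among n patients. Take the largest c with P(X ≤ c | n, p0) ≤ 0.01; that probability is the attained alpha. Power is P(X ≤ c | n, p1).

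| Landmark | p0 v p1 | Smallest n for 95% | n = 324 | n = 346 | n = 386 |
|---|---|---|---|---|---|
| 2.5 years | 3% v 0.5% | 383 | c = 2, alpha 0.0032, power 77.8% | c = 3, alpha 0.0072, power 90.3% | c = 4, alpha 0.0094, power 95.4% |
| 5 years | 4% v 1% | 396 | c = 5, alpha 0.0099, power 89.1% | c = 5, alpha 0.0055, power 86.4% | c = 6, alpha 0.0051, power 90.4% |
| 7.5 years | 6% v 1.5% | 263 | c = 9, alpha 0.0057, power 97.4% | c = 10, alpha 0.0059, power 98.3% | c = 12, alpha 0.0070, power 99.4% |

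Exact power is saw-toothed. At 5 years, n = 396 reaches 95.2%, n = 400 to 430 falls just below 95% again, and every n from 431 upward qualifies. For every n from 324 to 346, 5-year power lies between 86% and 89%.

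**The printed limit of 8, at 5 years.**
- n = 346: P(X ≤ 8 | 4%) = 0.063; P(X ≤ 8 | 1%) = 99.1%.
- n = 324: 0.097 and 99.4%.
- n = 386: 0.027 and 98.3%.

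Adding the first look (more than 5 of 144) lowers these alphas only to 0.061, 0.092 and 0.027.

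**If one 20% loss was meant.** 540 × 0.8 = 432. At 5 years c = 8, alpha 0.0096, power 96.8%, so the stated properties are met. At 2.5 years c = 4, alpha 0.0035, power 93.2%, slightly short.

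**The case against.** The strongest reply is that power is not lost under the protocol's own rule. A reader might infer from the table that the trial's 5-year power is simply 86%. That figure needs a cut-off of 5 relapses at the final analysis, which the article does not print. With its limit of 8, power on 346 patients is about 99%. This stands, and it moves the cost to alpha rather than removing it: type I error is then about 6%.

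A reader might also conclude that the sponsor inflated 386 by multiplication. The article never calls 386 an evaluable or pre-inflation number, only the count treated at the second analysis. The route through 431 fits 540, the limit of 8, and the stated alpha and power at least as well. The origin is therefore open. Neither route provides for both losses.

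Third, 346 may be too low. The 20% loss has no date and follow-up runs for 10 years. With all drop-out but half the loss by year 5, 540 × 0.8 × 0.9 = 388.8, about 389, remain. Power is then 90% (c = 6, alpha 0.0047), still below 95%. Kaplan-Meier curves (Study objectives) would use partial follow-up, but the primary efficacy section specifies a proportion and the decision limits are counts, so the number evaluable still matters.

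Finally, it is tempting to blame the whole gap on attrition. The figures do not support that: 386 fully evaluable patients give 90.4% at 5 years with alpha held, or alpha of 2.7% with the limit of 8. Part of the gap comes from which landmark is tested, and the article leaves that open.

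**Conclusion.** The point holds in a limited form. Read as two losses complete by the landmark, the stated 20% and 20% leave 324–346 of 540 patients. With one-sided alpha held at 0.01, power is about 86–89% at 5 years and 78–90% at 2.5 years, against a stated 95%. The 7.5-year comparison is covered. Under the printed limit of 8, 5-year power is kept and type I error is about 6% (346) to 10% (324), against a stated 1%.

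These are ranges under stated assumptions, not one power figure for the trial. A two-sided alpha of 0.01 would make the shortfall worse; slower loss would reduce it. If the two 20% figures describe one loss, 540 meets the 5-year target and the fault lies in the wording of the abstract and of Study hypothesis. The documents do not show that more patients must be recruited: restating what 540 delivers is enough.

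**What to change.** Keep 540. In the abstract and under Study hypothesis, state:
- the landmark that drives the size and the sidedness of alpha;
- how the two 20% losses combine and by when they are assumed to occur;
- the resulting evaluable number, and the alpha and power it delivers (about 86–89% at 5 years if alpha is held at 0.01 and both losses apply).

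If one 20% loss was meant, say so and give 432 evaluable, with 5-year alpha of 0.0096 and power of 96.8% at a cut-off of 8.

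State that the final efficacy cut-off is derived from the number actually evaluable at the landmark, so that alpha of 0.01 is held. Reconcile it with the relapse counts under Planned interim analysis and Investigator withdrawal. Whether those counts should change as stopping rules is for the sponsor to settle.

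The cost is wording and no extra patients. The downside is that, unless a single loss was meant, the stated power or the stated alpha becomes less favourable.

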### Description of the primary efficacy analysis and population

A single group of patients is studied. The proportion of patients who respond to treatment (i.e. local relapse free) will be used to estimate the true response rate with a 95% confidence interval. A response rate of 99.5%/99%/98.5% at 2.5/5/7.5 years is anticipated. A response rate of 97%/96%/94% is considered to be the minimum level.

Therefore, efficacy analyses will be performed at two stages.

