### Primary objectives

The primary objective is the rate of local relapse (within 2 cm around the tumor bed).

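### Three landmarks share one alpha, one power and one sample size, and none is named as deciding, so the stated type I error and power belong to no defined test

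*Protocol article*

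**What the plan says.** All references are to the protocol article.

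- **Primary objectives** defines the endpoint by location only: "The primary objective is the rate of local relapse (within 2 cm around the tumor bed"). No time point is given.
- **Description of the primary efficacy analysis and population** sets three anticipated levels, "A response rate of 99.5%/99%/98.5% at 2.5/5/7.5 years is anticipated", and three minimum levels, "A response rate of 97%/96%/94% is considered to be the minimum level". All three pairs have equal standing. The proportion free of local relapse "will be used to estimate the true response rate with a 95% confidence interval".
- **Study hypothesis** gives a single set of design figures: alpha 0.01, power 95% and 20% drop-out. Those figures together with "a loss to follow-up of 20% result in 540 patients to be included".
- **Planned interim analysis** schedules two looks: "The first after 144 patients and the second after 386 patients were treated". It repeats the three limits as relapse rates (3/4/6%) and converts them into two counts: efficacy is rejected with more than 5 relapses at the first look or more than 8 at the second. No follow-up time is attached to either count.

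No section, including the abstract, names the landmark that decides or says how the three results combine.

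**The concern.** The time point is part of the hypothesis. An alpha of 0.01 and a power of 95% describe a test of one stated null rate against one stated alternative. Here three such pairs are printed beside one alpha, one power and one N, so a reader cannot tell which test those figures describe. Three limits are also turned into two counts, so the counts cannot be matched to the landmarks one to one. The 95% interval does not settle the matter: used for a decision, it would correspond to one-sided 0.025, not 0.01.

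If the landmarks disagree, for example with a pass at 2.5 years and a failure at 5, the plan has no rule for the conclusion. The sponsor could then choose the landmark with the results in hand.

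**Working it through.** **Inputs.** Relapse probability at the minimum level, q0 = 0.03/0.04/0.06, and anticipated, q1 = 0.005/0.01/0.015, at 2.5/5/7.5 years; alpha 0.01; power 0.95; N = 540; looks at 144 and 386; rejection counts >5 and >8. Assumptions: alpha is one-sided (the article does not say), follow-up to each landmark is complete, and relapse counts are binomial.

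**1. The plan's own sample size.** Exact single-stage design: the smallest n for which some c satisfies P(Bin(n, q0) ≤ c) ≤ 0.01 and P(Bin(n, q1) ≤ c) ≥ 0.95.

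| Landmark | n | Relapses allowed |
|---|---|---|
| 2.5 years | 383 | 4 |
| 5 years | 396 | 7 |
| 7.5 years | 263 | 7 |

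The second look at 386 is close to both the 2.5-year result (3 more) and the 5-year result (10 fewer), and far from the 7.5-year result. Also 386 × (1 + 0.2 + 0.2) = 540.4, which reproduces 540. The sample size is therefore explained, but it does not reveal whether 2.5 or 5 years was meant.

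**2. Each landmark tested alone with 386 evaluable patients.** The cut-off is the largest c with P(Bin(386, q0) ≤ c) ≤ 0.01; power is P(Bin(386, q1) ≤ c).

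| Landmark | Cut-off | Attained alpha | Power |
|---|---|---|---|
| 2.5 years | ≤ 4 | 0.0094 | 0.954 |
| 5 years | ≤ 6 | 0.0051 | 0.904 |
| 7.5 years | ≤ 12 | 0.0070 | 0.994 |

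**3. The three landmarks together.** Cumulative relapse counts are nested. The count at 2.5 years is Bin(386, a). Given a count x there, new relapses by 5 years are Bin(386 − x, (b − a)/(1 − a)), and likewise from 5 to 7.5 years. Exact enumeration with cut-offs 4/6/12 gives:

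- anticipated rates: pass at 2.5 years and fail at 5 years, 0.065; pass at all three, 0.889;
- all rates at the minimum level: pass at one or more, 0.0159; pass at all three, 0.0013.

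**4. The protocol's own counts, read at one landmark.** P(efficacy not rejected) = Σ over i = 0 to 5 of P(Bin(144, q) = i) × P(Bin(242, q) ≤ 8 − i), where 242 = 386 − 144.

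| Landmark | Type I error (q0) | Power (q1) |
|---|---|---|
| 2.5 years | 0.177 | 0.9997 |
| 5 years | 0.027 | 0.981 |
| 7.5 years | 0.0002 | 0.864 |

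At 2.5 and 5 years the error exceeds 0.01; at 7.5 years the power falls short of 95%.

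**The case against.** **The stopping rule reads as if every limit must be respected.** The study stops if relapse exceeds 3/4/6% at the respective times, which more naturally means that all three must hold. Under that reading there is no inflation: false success is 0.0013. This stands. A reader might infer from three landmarks that the family of tests exceeds alpha 0.01. That is true only if passing any one landmark suffices (0.016), and the article does not say so. The all-must-pass reading is not stated either, and with 386 evaluable patients its power is 0.89, not 95%. With 540 evaluable patients (cut-offs 7/11/19) power would be 0.987, but that supposes no attrition, against the planned 20% drop-out and 20% loss.

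**The counts can only reject efficacy.** A reader might infer that the plan lets IORT be confirmed at 2.5 years. No sentence provides for that, and the primary analysis is an estimate with an interval. This also stands. Yet the stated hypothesis is to confirm non-inferiority and minimum levels are set, so some result must count as confirmation, and the article does not say which.

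**The 2.5-year limit may look the laxest.** At constant hazard, 3% at 2.5 years becomes 1 − 0.97² = 5.9% at 5 years, above the 4% limit. The protocol assumes no hazard shape for its minimum levels, which are tolerances and need not lie on one curve. The point does not rest on this.

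**The cut-offs 4/6/12 are not in the protocol.** Correct: they are what alpha 0.01 implies at 386. The protocol's own counts are therefore assessed separately in step 4.

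**A condensed article may leave the hierarchy to the full protocol or SAP.** A missing hierarchy alone would be a weak point. But the article prints alpha, power and rejection counts, and read at a single landmark these do not agree at any of the three.

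**Conclusion.** The point holds in this form: no deciding landmark and no combination rule is stated, so the quoted alpha of 0.01 and power of 95% are not properties of any defined test. The choice matters. Required evaluable numbers run from 263 to 396, power at 386 runs from 0.904 to 0.994, and the type I error of the protocol's own counts runs from 0.0002 to 0.177. Even if the treatment performs exactly as anticipated, a pass at 2.5 years with a failure at 5 years arises in 6.5% of trials, and the plan does not resolve it.

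These figures rest on a one-sided alpha, binomial counts, complete follow-up of 386 patients and, for the protocol's counts, both looks being read at the same landmark. They do not show that the trial's type I error exceeds 0.01 through multiplicity; that depends on a rule the article does not give. This should be corrected, but it does not by itself invalidate the design.

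**What to change.** 1. In Primary objectives and in the description of the primary efficacy analysis, name one deciding landmark. Five years, 1% anticipated against 4% minimum, is a reasonable choice.
2. State that the 2.5-year analysis can only reject efficacy and never confirm it. Make 7.5 years supportive, or test it at 0.01 only after 5 years has passed (fixed sequence).
3. In Planned interim analysis, tie the efficacy counts to the deciding landmark and restate the alpha and power they deliver. At 5 years with 386 patients, the existing rule (rejection above 8) gives alpha 0.027 and power 0.98; allowing at most 6 relapses gives alpha 0.005 and power 0.90. The sponsor should state which pair of figures it accepts.

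**Cost.** These are wording changes. No efficacy claim can be made from 2.5-year data, and the stated alpha or power becomes less favourable. No extra patients or visits are needed if the figures are restated. Keeping both 0.01 and 95% at 5 years would need 396 evaluable patients, about 555 enrolled with the plan's apparent inflation (396 × 1.4 = 554.4).
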